# A factorial randomized controlled trial to evaluate the effect of micronutrients supplementation and regular aerobic exercise on maternal endothelium-dependent vasodilatation and oxidative stress of the newborn

**DOI:** 10.1186/1745-6215-12-60

**Published:** 2011-02-28

## Abstract

**Background:**

Many studies have suggested a relationship between metabolic abnormalities and impaired fetal growth with the development of non-transmissible chronic diseases in the adulthood. Moreover, it has been proposed that maternal factors such as endothelial function and oxidative stress are key mechanisms of both fetal metabolic alterations and subsequent development of non-transmissible chronic diseases. The objective of this project is to evaluate the effect of micronutrient supplementation and regular aerobic exercise on endothelium-dependent vasodilation maternal and stress oxidative of the newborn.

**Methods and design:**

320 pregnant women attending to usual prenatal care in Cali, Colombia will be included in a factorial randomized controlled trial. Women will be assigned to the following intervention groups: *1. Control group: *usual prenatal care (PC) and placebo (maltodextrine). *2. Exercise group: *PC, placebo and aerobic physical exercise. *3. Micronutrients group: *PC and a micronutrients capsule consisting of zinc (30 mg), selenium (70 μg), vitamin A (400 μg), alphatocopherol (30 mg), vitamin C (200 mg), and niacin (100 mg)*. 4. Combined interventions Group: *PC, supplementation of micronutrients, and aerobic physical exercise. Anthropometric measures will be taken at the start and at the end of the interventions.

**Discussion:**

Since in previous studies has been showed that the maternal endothelial function and oxidative stress are related to oxidative stress of the newborn, this study proposes that complementation with micronutrients during pregnancy and/or regular physical exercise can be an early and innovative alternative to strengthen the prevention of chronic diseases in the population.

**Trial registration:**

NCT00872365.

## Background

In the last decades, it has been suggested that maternal factors such as endothelial function and oxidative stress are key mechanisms in fetal metabolic alterations and the subsequent development of non-transmissible chronic diseases [NTCD] in the adulthood [1].

In addition to the effect of these factors, other external factors such as lifestyle, physical activity, diet, and tobacco consumption could be involved in the development and progress of non-transmissible chronic diseases [1] However, the interaction between the maternal and the external factors during pregnancy that could be involved in the development and progression of NTCD remains unclear. Therefore, it is necessary to establish if maternal and external factors have influence on the placental function and on the neonatal metabolic alterations or both.

During pregnancy, several factors could affect the organization of fetal systems and sub-systems [2-4]. It has been proposed that interventions such as the supplementation with micronutrients and the practice of physical exercise could decrease the incidence or progression of NTCD, probably because both interventions have been reported to increase the synthesis of nitric oxide, a very important factor for the function of the vascular endothelium and for reduction of the oxidative stress [3-5].

This postulate has been primarily based on evidence that ingestion of some micronutrients (*e.g*, vitamin and minerals, among others, etc.) [6] and regular physical activity (at least of 12 weeks) [7], decreases oxidative stress [8] and restore endothelial function [9] in non-pregnant women [10]. However, the effect of these interventions have not been studied during pregnancy, although both are safe and economically feasible [11]. Furthermore, most studies have focused on measuring the effects on anthropometric measurements of neonate (*i.e.*, weight, height, among others) [12-14] despite the possible independent relationship between the endogenous factors and anthropometric characteristics [15-17].

The objective of this study is to determine the effect of the micronutrients supplementation and regular aerobic exercise during pregnancy on maternal endothelial function and neonatal oxidative stress. Furthermore, the effect of both interventions on the anthropometric parameters of the newborn will be evaluated. We expect that the results of this study will provide valuable information to design efficient public health policies during pregnancy aimed to prevent NTCD.

### Hypothesis

Supplementation with micronutrients or regular aerobic exercise improves endothelial function in the mother and reduces oxidative stress in newborn.

## Methods/Design

### Study Design

This is a single blind, randomized controlled 2 × 2 factorial trial designed to evaluate the effectiveness of micronutrients supplementation and regular aerobic exercise during pregnancy. This design provides the advantage of assessing the independent and cumulative effects of the interventions in nulliparous pregnant women.

### Interventions

All women included in the study will receive usual prenatal care according to WHO guidelines. The following intervention groups will be compared:

#### 1. Control Group

This group will receive the usual prenatal care according to both WHO and Colombian guidelines and placebo (maltodextrine). In Colombia, pregnant women receive ferrous sulphate, calcium, and folic acid during prenatal care. In addition, they receive counselling about breastfeeding, key signs and symptoms, diet and screening for pregnancy diseases. The Colombian guidelines do not include physical exercise prescription during pregnancy neither counselling from a physical therapist [18].

#### 2. Exercise Group

Regular aerobic exercise: walking (10 minutes), aerobic exercise (30 minutes), stretching (10 minutes), and relaxation exercises (10 minutes) during a three-month period. Exercise will be performed during 3 sessions per week. A physical therapist and a physical educator will supervise all sessions. The exercise-program is according to the American College of Obstetrics and Gynecology (ACOG) [18] and the American College of Sports Medicine (ACSM) exercise prescription [19]. Aerobic activities will be performed at moderate intensity (60-70% of maximal heart rate) measured by the 6-20 Borg's rating scale (PER). Each session will start with a 5 min warm up, followed by 30 min of aerobic activity, including a 5 min cool down. Subsequently, a 15 min strength training for upper limbs, lower limbs, and deep abdominal muscle stabilization. The last 5 min consist of stretching and relaxation exercises. (Table 1)

**Table 1 T1:** Pregnancy 2 X 2 Factorial Design

	Regular Physical Exercise	
	
	-	+
**Micronutrients**		
-	Usual Prenatal Care + Placebo	Usual Prenatal Care + Regular physical exercise
+	Usual Prenatal Care + Micronutrients Supplementation	Usual Prenatal Care + Regular physical exercise + Micronutrients Supplementation

#### 3. Micronutrients Supplemental Group

This group will receive supplementation of zinc (30 mg), selenium (70 μg), vitamin A (400 μg), alphatocopherol (30 mg), vitamin C (200 mg), and niacin (100 mg).

#### 4. Combined interventions Group

This group will receive both the supplementation with micronutrients and physical exercise as described above.

### Sample size

Measurement of endothelial function (FMD), validated in several population studies was selected as the critical variable to calculate the sample size. Sample size was conservatively calculated to detect all six pairwise difference between treatment groups with a Bonferroni adjustment for an overall 0.05 type I error (0.05/6 = 0.0083) [20]. A sample size of 320 subjects or 80 per treatment group was estimated. The sample size was calculated assuming a specific difference between the groups of 4.3% in the FMD after 3 months of treatment with 11 of maximum standard deviation. It was accepted a type I error of 0.05, a power of 80%, and it was adjusted by 20% [20].

Eligible women for the present study and those interested in participating will be invited to a pre-test that includes an interview (Visit A) and further assessments that will be performed at the Red de Salud Ladera (Hospital Cañaveralejo, Centro de Salud Meléndez, Centro de Salud Siloé, Hospital Universitario del Valle) and at the Laboratory of Biochemistry of the Universidad of Valle, Cali-Colombia. The first visit will take place between weeks 12 and 20 (Visit B), the second at week 32 and 36 (Visit C) and the last one, after delivery (Visit D).

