### Outcome variables

1. The primary outcome is the change of endothelium-dependent brachial artery flow-mediated dilatation (FMD) after three months of regular aerobic exercise. [Time Frame: Baseline and 32 to 36 weeks of gestation].

2. The secondary outcome is the concentration of F2-isoprostanes in umbilical cord blood of newborn [Time Frame: Delivery].

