### Analytic plan

All pregnant women studied will be analyzed according to original group allocation and all changes in outcome variables will be attributed to the assigned treatment. An exploratory analysis will be performed to determine frequency, range, variability, and distribution type for each variable in order to use the most appropriated statistical test when comparisons will be necessary. Subsequently, a descriptive analysis of the socio-demographic characteristics, gestational variables, and baseline measures (x_0_) will be performed for each comparison group. These analyses permit to assess the primary analysis of the data and will be undertaken using the principle of intention-to-treat (ITT). The ITT analysis for this study will include all participants, including those who are not fully compliant and those with missing outcome data. While we plan to implement procedures to minimize loss to follow-up and patient withdrawal, we expect to observe some attrition. We plan to employ multiple imputations to handle missing data in the analysis. Multiple imputations, compared to other case deletion strategies, can provide valid inferences with less restrictive assumptions surrounding the mechanism for missing data [21-23].

Due to that this is an experimental design with two measures of the maternal outcome variable, the first at baseline x_0 _(t_0 _= 16-20 gestational weeks) and the second after interventions x_1 _(t_1 _= 32-36 gestational weeks) in four study groups, a comparative analysis between these measures to establish differences will be executed. In order to perform these comparisons one way ANOVA [24] or Kruskal-Wallis [25] tests will be applied, if appropriated. Subsequently, a multivariate analysis will be carried out and the autocorrelation between repeated measures will be taking in to account. We will use longitudinal analysis methods such as GEE in order to control the differences among measures at baseline and to incorporate incomplete observations into this analysis [26].

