In order to evaluate the effects of maternal regular physical exercise and micronutrients supplementation on newborn's oxidative stress (concentration of F_2_-Isoprostanes in umbilical cord blood), a comparative analysis will be executed to establish if the effects are different among study groups using analysis of covariance (ANCOVA), a form of general linear model [26]. We will include the baseline measure as a covariate in the model and pre-specified potential confounding factors: maternal age, previous physical exercise level, tobacco or alcohol consumption, differences in diet report and pregnancy complications such as hypertension and diabetes [26]. These will be included regardless of whether baseline imbalance exists. This approach has been chosen because confounder selection strategies that are based on collected data can result in models with poor statistical properties [26]. This will adjust appropriately for any baseline imbalance and will provide the most powerful analysis. Adjusted estimates of intervention effect from this model will be reported as the primary analysis in the trial publication.

Finally, we will investigate if there is an interaction between the two interventions for the primary outcome at 32 gestational weeks (regular physical exercise) or until the birth (micronutrients supplementation). For these analyses we will include appropriate interaction terms in the models [26]. The trial is not powered to detect these interactions and is likely to have poor precision for the interaction terms. We plan to report regression coefficients for the interaction terms and their 95% confidence intervals.

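### With the plan's own inputs, 80 women per group give about 33–43% power, not 80%, for the six pairwise FMD comparisons at 0.0083, and the named FMD analyses do not identify a primary contrast

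*Protocol article*

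**What the plan says.** The Sample size section of the protocol article bases the trial on FMD and on detecting "all six pairwise difference between treatment groups with a Bonferroni adjustment for an overall 0.05 type I error (0.05/6 = 0.0083"). The inputs are given as "assuming a specific difference between the groups of 4.3% in the FMD after 3 months of treatment" "with 11 of maximum standard deviation". The section continues "It was accepted a type I error of 0.05", then "a power of 80%, and it was adjusted by 20" per cent. It does not state what the 20% is for or whether tests are one- or two-sided. The result is 80 women per group, 320 in all.

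For maternal FMD at baseline and at 32–36 weeks, the Analytic plan says that "one way ANOVA [24] or Kruskal-Wallis [25] tests will be applied, if appropriated". It then describes a longitudinal model such as GEE, to handle baseline differences and incomplete observations. Interaction terms between the two interventions will be reported with 95% confidence intervals, and the article says the trial is not powered for them. The Study Design section describes a 2 × 2 factorial trial.

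**The concern.** The section makes a specific promise: 80% power for every pairwise difference while the overall type I error is held at 0.05. With an SD of 11 and a difference of 4.3, the standardised difference is 4.3/11 = 0.39. That is modest for 80 per group at a per-test level of 0.0083, so the figure needed checking.

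If the power is much lower than stated, most pairwise differences of the planned size would be missed, and a reader could take a non-significant contrast as evidence of no effect. Switching to another FMD analysis would not settle this, because the article does not say which FMD contrast carries the main conclusion. A 2 × 2 design allows comparisons of 160 with 160, and the sizing makes no use of them.

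**Working it through.** **Inputs** (Sample size section): difference d = 4.3; SD s = 11; per-comparison alpha 0.05/6 = 0.0083; power 80%; four equal groups of 80; 20% adjustment. **Assumptions:** two-sided tests, normal approximation, d and s both in absolute FMD points, and s applying to the measure analysed.

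**1. Trying to reproduce 80 per group.** n per group = 2(z_alpha + z_power)² s²/d², with s²/d² = 121/18.49 = 6.544 and z_power = 0.842.

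| Per-comparison alpha | z_alpha | n per group | Total | n per group after /(1 − 0.2) |
|---|---|---|---|---|
| 0.0083 two-sided | 2.638 | 159 | 636 | 199 |
| 0.0083 one-sided | 2.394 | 138 | 552 | 173 |
| 0.05 two-sided | 1.960 | 103 | 412 | 129 |
| 0.05 one-sided | 1.645 | 81 | 324 | 102 |

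For the first row: 2 × (2.638 + 0.842)² × 6.544 = 158.5, rounded up to 159. Of these variants, only the one-sided 0.05 calculation comes near 80 per group, and it omits both the Bonferroni and the 20% adjustments that the section says were made.

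**2. Power of one pairwise comparison at two-sided 0.0083.** Power = Φ(d/SE − 2.638), with SE = 11√(2/n).
- n = 80: SE = 1.739; 4.3/1.739 = 2.472; Φ(−0.166) = 0.43 (0.42 by the noncentral t).
- n = 64 (80 × 0.8): SE = 1.945; 4.3/1.945 = 2.211; Φ(−0.427) = 0.33 (0.32 by the noncentral t).

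For 80% power at 0.0083, the detectable difference is 6.05 points with 80 per group and 6.77 with 64. Alternatively, with d = 4.3 the SD would have to be about 7.8 (n = 80) or 7.0 (n = 64).

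**3. What the named omnibus test addresses.** A four-group F-test at 0.05 with 80 per group has power of:
- 52% if two groups differ by 4.3 and the other two lie midway;
- 71% if one group differs from the other three by 4.3;
- 84% if there is a single main effect of 4.3.

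Its power depends on the pattern of the four means, and on its own it does not test the six pairwise hypotheses.

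**4. Factorial main effects, two-sided 0.025 each.** z_alpha = 2.241; SE = 11√(2/160) = 1.230, or 11√(2/128) = 1.375.

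| True pattern | Main effect | 160 v 160 | 128 v 128 |
|---|---|---|---|
| 4.3 is the full main effect, no interaction | 4.3 | Φ(3.497 − 2.241) = 0.90 | Φ(3.127 − 2.241) = 0.81 |
| Only one cell differs by 4.3 | 4.3/2 = 2.15 | Φ(1.748 − 2.241) = 0.31 | Φ(1.564 − 2.241) = 0.25 |

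**The case against.** The best defence has three parts.

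First, a journal article need not list follow-up contrasts. An omnibus test followed by Bonferroni comparisons is a common sequence, a GEE model with group terms can supply pairwise contrasts, and a SAP that is not shown may say so. This stands: the absence of 0.0083 from the Analytic plan would not be a fault by itself. It does not rescue the power statement, which is fixed in the article and does not follow from its inputs.

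Second, the SD of 11 is called a maximum, and adjusting for baseline FMD would reduce the residual SD. That is fair, but the required SD of 7.8 or 7.0 implies a baseline–follow-up correlation of about √(1 − (7.8/11)²) = 0.70, or √(1 − (7.0/11)²) = 0.77. The article states neither a correlation nor such an adjustment in the sizing.

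Third, the main-effect figures flatter the alternative. This also stands, and the one-cell case is shown above for that reason.

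A reader might infer more than the documents support:
- **That the overall error rate is uncontrolled.** This would require six unadjusted tests at 0.05. The article never proposes them; it specifies Bonferroni.
- **That "Adjusted estimates of intervention effect from this model will be reported as the primary analysis in the trial publication" names a rival FMD analysis.** That sentence closes the paragraph on the ANCOVA for cord-blood F2-isoprostanes, the secondary outcome, so it does not bear on the FMD contrasts.
- **That "after three months of regular aerobic exercise" in the outcome definition makes exercise the only confirmatory contrast.** It describes the outcome and its timing and selects no comparison. The objective and hypothesis name both interventions.

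**Conclusion.** The point holds as a misstatement of power together with an unidentified primary FMD contrast. Against a stated 80%, each pairwise comparison at 0.0083 has about 43% power with 80 per group, or about 33% if 20% are lost. The planned 80 is about half of the 159 per group required before any adjustment.

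The 33% figure depends on reading the 20% as attrition; the 43% does not. Both assume two-sided testing, but the conclusion does not depend on that, since one-sided tests at 0.0083 still need 138 per group.

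The documents do not show that the omnibus test and GEE exclude pairwise follow-up, or that error control has been given up. They show that the contrasts used for sizing are not delivered at the stated power, and that the article leaves open which FMD contrast is primary.

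**What to change.** In the Sample size section, restate the pairwise power at 0.0083 as about 33–43%, and state sidedness and what the 20% adjustment is for.

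In the Sample size section and the Analytic plan alike, name the exercise and micronutrient main effects on FMD as the primary contrasts with a stated alpha, for example two-sided 0.025 each for an overall 0.05. Label the six pairwise contrasts at 0.0083 as supportive and outside that overall 0.05, so that the same error is not spent twice.

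Report main-effect power with its condition: about 90% (160 v 160) or 81% (128 v 128) only if 4.3 is the full main effect without interaction, and about 31% or 25% if only one cell differs by 4.3.

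The cost is a change of wording with no added participants. There are two drawbacks. The published pairwise power becomes less favourable. Main effects also average over the other factor, so they must be read with the interaction estimate that the Analytic plan already intends to report and already describes as imprecise.

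### On the stated inputs, each Bonferroni-adjusted pairwise comparison needs about 160 women per group before losses, not 80; power with 80 per group is about 42%, not 80%

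*Protocol article*

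**What the plan says.** The whole calculation stands in one paragraph of the protocol article, under Sample size.

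- Comparisons and error rate: "Sample size was conservatively calculated to detect all six pairwise difference between treatment groups with a Bonferroni adjustment", with the level per comparison given as 0.05/6 = 0.0083.
- Effect and spread: a "difference between the groups of 4.3% in the FMD after 3 months of treatment with 11 of maximum standard deviation".
- Error, power and allowance: "It was accepted a type I error of 0.05, a power of 80%, and it was adjusted by 20" per cent.
- Result: "A sample size of 320 subjects or 80 per treatment group was estimated".

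The paragraph does not say whether tests are one- or two-sided. It does not say whether 11 is the SD of FMD at one visit or of its change, and it gives no baseline to follow-up correlation. Under Outcome variables, the primary outcome is the change in FMD from baseline to 32 to 36 weeks. The Analytic plan compares the four groups by one-way ANOVA or Kruskal-Wallis, then by GEE with control for baseline differences, and expects some attrition. It warns of low power only for the interaction between the two interventions.

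**The concern.** Every quantity needed for a two-sample calculation is given, so the result can be checked directly. A standardised difference of about 0.39 tested at 0.0083 cannot be detected with 80% power in groups of 80. Detail left to a fuller protocol would not explain this, because the inputs and the answer are printed together and disagree.

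The primary outcome is affected. A reader of the eventual results would take the pairwise comparisons to have 80% power for 4.3 points, and might read a null comparison as evidence against an effect of that size. On the stated inputs, a true 4.3-point difference between two groups would more often be missed than found. The article also calls the calculation conservative, which discourages anyone from checking it.

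**Working it through.** **Inputs (Sample size section).** Difference 4.3; SD 11; level 0.05/6 = 0.00833; power 0.80; 20% adjustment; four equal groups. Two-sided testing is my assumption. The 20% is taken as an allowance for losses, so 80 randomised leaves 80 × 0.8 = 64 evaluable.

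**Step 1: try to reproduce 80 per group.** Standardised difference d = 4.3/11 = 0.391.

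Normal approximation: n per group = 2 × (z₁₋α/₂ + z₀.₈₀)² × (SD/difference)²
= 2 × (2.638 + 0.842)² × (11/4.3)²
= 2 × 12.11 × 6.544 = 158.5, so 159.

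The t-test gives 160.2. With the 20% adjustment this becomes 160.2/0.8 = 200.3, or 160.2 × 1.2 = 192.3. The stated 80 is not reproduced.

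**Step 2: other readings of the same inputs (t-test).**

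| Level per comparison | n per group before losses | n/0.8 | Power, 80 evaluable | Power, 64 evaluable |
|---|---|---|---|---|
| 0.0083 two-sided | 160.2 | 200.3 | 42% | 32% |
| 0.0083 one-sided | 138.5 | 173.1 | 52% | 42% |
| 0.05 two-sided | 103.7 | 129.6 | 69% | 59% |
| 0.05 one-sided | 81.6 | 102.0 | 79% | 71% |

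Only the last row comes near 80 per group. It does so by dropping both the Bonferroni adjustment and the 20% allowance, which the section says were applied.

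Normal-approximation check of the first row: power ≈ Φ(d√(n/2) − 2.638). For n = 80 this is Φ(2.472 − 2.638) = 43%; for n = 64 it is Φ(2.211 − 2.638) = 33%. Both are within about one point of the t-test.

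**Step 3: what 80 per group can detect.** At two-sided 0.0083 with 80% power, the detectable difference is 6.1 points with 80 evaluable and 6.9 points with 64.

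**Step 4: what would rescue 4.3 points.** The residual SD would have to be 7.7 (n = 80) or 6.9 (n = 64). If 11 is the SD of a single FMD measurement, baseline-adjusted analysis has residual SD 11 × √(1 − r²), so r = √(1 − (7.73/11)²) = 0.71, or √(1 − (6.89/11)²) = 0.78. A simple change score, with SD 11 × √(2(1 − r)), needs r of about 0.75 or 0.80.

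**Step 5: the factorial margins.** Pooling over the other factor compares 160 with 160, or 128 with 128 after 20% loss.

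| Marginal difference | Level per factor | 160 v 160 | 128 v 128 |
|---|---|---|---|
| 4.3 | 0.05 | 94% | 88% |
| 4.3 | 0.025 | 89% | 81% |
| 2.15 | 0.05 | 41% | 34% |

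The last row is the case where each intervention alone gives 4.3 and the combination also gives only 4.3. Each factor's effect is then 4.3 in one stratum and 0 in the other, so the marginal difference is (4.3 + 0)/2 = 2.15.

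**The case against.** The best case for the plan has several parts.

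- **The power figures are conditional.** Sidedness is not stated, 11 is described as a maximum SD, and the analysis will control for baseline. All of this stands and limits how firmly 42% and 32% can be put. It does not restore 80 per group: one-sided testing still gives only 52% and 42%, and neither the smaller SD nor the correlation of 0.7 to 0.8 is documented.
- **Not every pair need differ by 4.3.** If the two effects add, combined versus control differs by 8.6, and power at 0.0083 is 99% (80 per group) or 96% (64). True, but the paragraph claims 80% power at a difference of 4.3, and that is what fails.
- **The Analytic plan never specifies the six pairwise tests.** Also true. That leaves the sample size attached to comparisons which the analysis text does not name, so it does not repair the calculation.

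Three stronger readings are tempting and should not be drawn.

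- A reader might call the target incoherent, since four means cannot all lie 4.3 apart. The natural reading of the paragraph is a smallest difference to detect in any one comparison, which is coherent.
- A reader might infer that 320 is a two-group total of 2 × 160 spread over four groups. The document does not show this. The exact totals are 318 (normal, 2 × 159) or 322 (t-test, 2 × 161), and other routes lead to about 80, such as the one-sided unadjusted calculation or a one-sample formula (79.2).
- A reader might conclude that 320 women are comfortably enough because the main effects have 94% power. That holds only without interaction, which the article plans to examine and says it is not powered to detect.

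**Conclusion.** The stated sample size does not follow from the stated inputs, and the statement must be corrected. Before losses the shortfall is a factor of about two (160 against 80 per group). After the 20% adjustment it is about 2.4 to 2.5 (192 to 200 against 80). The claimed 80% power per pairwise comparison is about 42% with 80 evaluable per group and about 32% with 64.

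These figures rest on two-sided testing, on 11 being the SD of the quantity compared, and on the 20% being an allowance for losses. They apply to each comparison singly; detecting all six together is no more likely than detecting any one. The finding concerns the pairwise claim. It does not show that 320 women are too few for every purpose of a factorial trial.

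**What to change.** Keep N = 320 and rewrite the Sample size paragraph.

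1. Delete the claim of 80% power for all six pairwise comparisons, and the word conservatively.
2. State the sidedness, and whether the SD of 11 refers to FMD or to its change. If baseline adjustment is relied on, state the assumed correlation and its source.
3. Report the pairwise comparisons as they are: at two-sided 0.0083, about 42% power for 4.3 points with 80 evaluable per group and about 32% with 64, and detectable differences of 6.1 and 6.9 points.
4. If the sponsor wants the factorial main effects to justify 320, say so and give the power for 4.3 points: 89% (81% after 20% loss) at 0.025 per factor, which keeps the overall 0.05, or 94% (88%) at 0.05 per factor, which does not. State that this assumes no interaction, and show the 2.15-point case (41%, or 34% after loss, at 0.05). Align the Analytic plan, which now specifies one-way ANOVA or Kruskal-Wallis across four groups.

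Items 1 to 3 cost a rewritten paragraph and no extra participants, but the stated pairwise power becomes less favourable. Item 4 is a design choice for the sponsor and also requires a change to the analysis text.
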